### Outcomes and assessments

Participant study samples will be shipped in batches to a central laboratory, where they will be analysed using liquid chromatography with tandem mass spectrometry (LC-MS/MS) assays to determine the levels of serum cortisol, salivary cortisol and salivary cortisone present at each timepoint.

Mean serum cortisol concentrations measured at baseline and at 30 min following stimulation with Nasacthin and Synacthen, as well as mean change from baseline, will be compared for non-inferiority, and will also be used to determine the proportion of participants for which the Nasacthin test produces a rise above a preset threshold, out of those for whom the Synacthen test also produces a rise above the threshold. The mean change from baseline in serum cortisol concentration at baseline and 30 min after Nasacthin and Synacthen stimulation will also be separately compared against their respective placebo drugs to determine superiority.

Mean serum cortisol concentrations and mean change in serum cortisol from baseline after Nasacthin and Synacthen stimulation will additionally be compared using values obtained at baseline and 60 min after drug administration, while mean salivary cortisone concentration and mean change from baseline in salivary cortisone will be similarly compared using the baseline and 60 min after Nasacthin and Synacthen administration timepoints.

Although the aim is to attain a complete set of glucocorticoid results for all samples for all participants across the four study visits, it is not essential in this study for a participant to provide a viable sample for every timepoint at each individual visit. It is, however, vital that those samples critical to the determination of the main study endpoints should be collected in order to ensure sufficient data for the primary and secondary analyses. The baseline and 30 min serum samples are crucial for the primary non-inferiority analysis, for the calculation of the NPA and for the comparisons between active and placebo treatments. The baseline, 30 min and 60 min serum samples are necessary for the secondary non-inferiority analyses, and the baseline and 60 min saliva samples are required to define the salivary cortisone response. The remaining salivary samples will be used for the additional PD analysis to calculate the elimination of cortisol; the minimum requirement for this is the 120 min saliva sample, plus two other samples from the later timepoints up to 480 min.

Individual visits will be repeated if viable key samples for endpoint determination are not obtained (eg, in the instance of cannula failure after IMP administration; blood contamination in saliva samples; unable to produce sufficient saliva for primary samples due to a temporary reason). In this instance, the same IMP will be administered at consecutive visits to ensure the randomised IMP sequence is maintained.

Participants will be closely monitored for any AEs occurring after IMP administration, particularly in the first 30 min, as this is when the majority of hypersensitivity reactions would be expected to occur. A follow-up telephone call 24–48 hours (or next available working day) after will be used as a safety check for any AEs occurring. All AEs, serious adverse events (SAEs) and suspected unexpected serious adverse reactions (SUSARs) will be collected in the study database and coded using the Medical Dictionary for Regulatory Activities (MedDRA), and reported as appropriate.

Participants will be asked to complete a non-validated questionnaire at the end of each visit to explore the acceptability and tolerability of IMP received at that visit and associated study sampling procedures. An additional final questionnaire at the end of their study completion will ask about their overall acceptability and tolerability, comparing both the nasal and intravenous tests.

Towards the end of their involvement in the study, participants will also be invited to take part in an optional one-to-one interview to gain a more in-depth understanding of their views on the acceptability and tolerability of the tests. A purposive sample of those who have given consent to be contacted will be used, with sampling criteria including age and gender, and whether all visits and study sampling were completed. At the end of study recruitment, participating healthcare professionals will be asked to complete an anonymous questionnaire on the comparative acceptability of administration of the two tests.

### Data collection and management

The main study database will be developed and managed by Hull Health Trials Unit (HHTU; University of Hull, Hull, UK) within the HHTU instance of commercial online data capture and randomisation system (RCC). The database will be built and validated according to study-specific requirements with both automated and manual checks to monitor data quality and completeness according to a sponsor-approved data monitoring plan.

The majority of data collected will be inputted directly into eCRFs in the study database. Participant views on the acceptability and tolerability of the tests will be recorded on paper questionnaires and then entered at site into RCC. Participant interviews will be audio or video recorded and transcribed verbatim. Audio/video recordings and the resulting anonymised transcripts will be held in the secure HHTU instance of Box.com collaborative cloud file storage system.

The e-Consent information will be collected using DocuSign Powerforms, located within a subaccount of the HHTU instance of e-signature platform DocuSign.

RCC data will be exported and transferred to the study statistician at the University of Sheffield and the qualitative researcher at Sheffield Teaching Hospitals NHS Foundation Trust for analysis, or for Data Monitoring and Ethics Committee (DMEC) reporting in compliance with the General Data Protection Regulation Act (GDPR 2018).

### Statistical analysis

#### Blind data review

Glucocorticoid values relating to each batch of study samples analysed will undergo a quality assurance check by the study statistician before the final dataset is provided. Individual visit data will be treated as completely independent (no within-participant linkage across visits) with original participant ID numbers removed from the dataset to preserve blinding. Spaghetti plots of all timepoints within each visit will be created. Any anomalies noted will be explored and resolved prior to database lock.

#### Interim go/no go analysis

A go/no go assessment point will be scheduled approximately halfway through the recruitment phase. The independent Trial Steering Committee will consider data on retention rates and the percentage of participants completing adequate samples for cortisol exposure analysis, and will advise whether the trial should continue.

#### Final analysis

Continuous data will be summarised using n, mean, SD, median, minimum and maximum, and lower and upper quartiles will be calculated as necessary. Demographics and any baseline characteristics will be summarised overall for the safety analysis set. Medical history, which will not be coded, will be listed but not summarised.

All available data will be included in each analysis. For example, comparisons of active versus placebo treatments will include all participants providing samples following receipt of both treatments at the required timepoints, while the safety analysis will include all participant visits in which Nasacthin (active) was administered. A participant does not need to have provided data at every timepoint after every treatment to be included in the analysis, therefore it is possible that the number of participants included in each analysis may vary.

The non-inferiority in absolute serum cortisol levels at 30 min between 500 µg Nasacthin and 250 µg Synacthen will be assessed using a one-sided test, in which the difference in paired means will be compared with a prespecified non-inferiority margin of −88 nmol/L, to ensure that the response to Nasacthin is, on average, no more than 88 nmol/L lower than that to Synacthen. This non-inferiority limit (maximum clinically acceptable difference in cortisol response) is based on published within-participant repeatability of the Nasacthin test,^11^ as agreed with the MHRA, with some adjustment to allow for additional variation in the baseline cortisol due to absence of dexamethasone suppression in these participants.

The superiority outcomes (superiority of active over placebo treatment) will be assessed using change from baseline levels by comparison of the paired means using two-sided t-tests and a significance level of 5% (0.05). CIs will also be produced.

The significance level (alpha) used for the non-inferiority test has been nominally set at 0.025, but will be determined by the results of the tests of the superiority primary objectives. This analysis will include all participants providing samples 30 min after receipt of both active treatments. The closely related secondary objective to demonstrate non-inferiority in serum cortisol levels using change from baseline levels instead of absolute values will be analysed using the same methodology.

The NPA, defined as the proportion of participants for which the Nasacthin test produces a rise above a predefined threshold (430 nmol/L) in serum cortisol at 30 min, using response to Synacthen as the reference standard, will be compared with 77.5% using a one-sided exact test, and an exact CI will also be provided. The significance level (alpha) used for the test has been nominally set at 0.025, but again will be determined by the results of the tests of the superiority primary objectives.

The secondary objectives to demonstrate non-inferiority in serum cortisol and salivary cortisone levels between 500 µg Nasacthin and 250 µg Synacthen will use the same methodology as the primary non-inferiority objective; however, they will use the 60 min timepoint and, for salivary cortisone, the non-inferiority margin will be set at ±25 nmol/L. Again, this non-inferiority margin is based on the published repeatability coefficient of previous work,^11^ with adjustment for the lack of dexamethasone suppression.

For the safety analysis, all participant visits in which Nasacthin (active) was administered will be included in the analysis. Any AEs reported in association with administration of placebo or Synacthen will be summarised as a comparison. AEs, SAEs and SUSARs will be summarised by treatment received, system organ class and preferred term.

For the exploratory objective, the serum cortisol, salivary cortisol and salivary cortisone responses at 30 and 60 min after each of the active treatments will be summarised using n, mean, SD, median, minimum and maximum.

A statistical testing hierarchy will be employed to ensure the overall 5% significance level is maintained for primary and secondary outcomes. First, the superiority primary outcomes will both be tested using α=5%. Both must be significant in order to continue; if both are significant, then the non-inferiority and NPA primary outcomes will be tested using a truncated Hochberg procedure to maintain a nominal 5% significance level. If at least one of these meets the criteria for significance, then secondary outcomes for non-inferiority will be tested using Hochberg procedure to maintain a nominal 5% significance (using available alpha after testing the primary objectives).

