### Sample size

A sample size of 30 participants was calculated as required to provide >90% power for the non-inferiority primary objective, assuming a non-inferiority margin of −88 nmol/L (equivalence limits of serum cortisol ±88 nmol/L) (as determined from previous work^11^ but with allowance for additional variation in baseline cortisol due to the absence of dexamethasone suppression) and a conservative significance level of α=2.5% (actual alpha to be defined by the truncated Hochberg procedure as part of a hierarchical testing procedure). The same sample size will have >90% power to show a negative percent agreement (NPA) >77.5% assuming a conservative α=2.5% and a one-sided exact test, and >90% power for the tests of superiority assuming a clinically relevant difference in serum cortisol change from baseline of 200 nmol/L and an SD of up to 70 nmol/L and α=5%.

The overall sample size was increased to 32, to allow for up to two participants who do not meet the requirement of a rise above threshold following Synacthen (or are excluded from the trial analysis for some other reason; eg, incomplete data).

Based on experience from previous studies, a dropout rate (including need for repeat visits in willing participants; eg, for cannula failure) of 33% in children and 20% for adults has been factored into the calculations, and therefore the overall recruitment target is 44 participants.

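### The primary non-inferiority test compares 30 min cortisol without using the pre-dose cortisol from the same visits: valid, but it gives up precision that is available at almost no cost

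*Protocol article*

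**What the plan says.** **The test.** Protocol article, Final analysis: "The non-inferiority in absolute serum cortisol levels at 30 min between 500 µg Nasacthin and 250 µg Synacthen will be assessed using a one-sided test". The statistic is the mean within-participant difference, set against −88 nmol/L; the article's wording is "in which the difference in paired means will be compared with a prespecified non-inferiority margin". Everyone with 30 min samples after both active treatments is included. No baseline term is given and no baseline sample is required. Non-inferiority on change from baseline is a separate secondary objective.

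**The baseline sample.** Study procedures has a paired blood and saliva sample drawn just before dosing at every visit. Outcomes and assessments states: "The baseline and 30 min serum samples are crucial for the primary non-inferiority analysis", in a sentence that goes on to the negative percent agreement (NPA) and the active-versus-placebo comparisons. Visits that fail to yield viable key samples are repeated.

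**Baseline variation.** The margin derives from earlier repeatability data and was settled with the MHRA. The article adds that it was set "with some adjustment to allow for additional variation in the baseline cortisol due to absence of dexamethasone suppression in these participants". Sample size says the same.

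**Power.** Sample size: "A sample size of 30 participants was calculated as required to provide >90% power for the non-inferiority primary objective". The inputs named there are the margin ("assuming a non-inferiority margin of −88 nmol/L") and a nominal 2.5% level. No SD or true difference is given for this test. The only SD stated belongs to the superiority tests: "a clinically relevant difference in serum cortisol change from baseline of 200 nmol/L and an SD of up to 70 nmol/L and α=5"%.

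**The concern.** Participants are not dexamethasone suppressed and are sampled near the morning cortisol peak. Pre-dose cortisol will therefore differ between a participant's two active visits, and part of that difference is likely to carry into the 30 min values. The protocol recognises this noise but deals with it through the margin. The margin is meant to be the largest tolerable mean shortfall, and random visit-to-visit variation does not change what shortfall is tolerable. It enters the standard error, and the natural place to remove it is the analysis, using a measurement already in hand.

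The secondary change-from-baseline analysis does not do this job. It fixes the baseline slope at 1, which can add noise, and it is reached only after the testing gates are passed.

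The article also gives two accounts of the baseline sample: crucial to the primary non-inferiority analysis in one section, and without a role in it in another. At stake is the width of the primary confidence interval, not its validity.

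**Working it through.** **Inputs from the article:** n=30, margin −88 nmol/L, one-sided 2.5% (nominal; the final level follows from the truncated Hochberg procedure), power above 90%.

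**Assumed, because not stated:** SD of the paired 30 min difference (SD), true mean difference (Δ), and rho, the correlation between the baseline difference and the 30 min difference across the two active visits.

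**1. The stated power.** For a paired t-test with 29 df, the noncentrality is (88 + Δ)/(SD/√30). Without an SD the stated power cannot be reproduced, so I solved for the largest SD that still gives 90%:
- Δ = 0: 143.7 nmol/L
- Δ = −20: 111.0 nmol/L
- Δ = −44: 71.8 nmol/L
- Δ = 0 at one-sided 1.25%: 130.8 nmol/L

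The claim is attainable but cannot be verified.

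**2. Raw power at two assumed SDs, Δ = 0.**
- SD 140: SE = 140/√30 = 25.6; noncentrality 88/25.6 = 3.44; power 91%.
- SD 100: SE = 100/√30 = 18.3; noncentrality 88/18.3 = 4.82; power above 99%.

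**3. Effect of adjustment.** Regress the paired 30 min difference on the paired baseline difference and test the intercept against −88. Residual SD is SD × √(1 − rho²), with 28 df.
- Variance removed, rho²: 0.3² = 9%, 0.5² = 25%, 0.7² = 49%. (In SD terms the last is √(1 − 0.49) = 0.71; the residual share is 51%, so the removal at rho 0.7 is 49%.)
- Sample size giving the same precision, 30 × (1 − rho²): 27.3, 22.5 and 15.3, so about 28, 23 and 16.

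**4. Simulated power** (20,000 trials per setting, bivariate normal differences, equal SDs):

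| SD, Δ | raw | adjusted, rho 0.3 | rho 0.5 | rho 0.7 |
|---|---|---|---|---|
| 140, 0 | 91% | 92–93% | 96% | 99% |
| 143.7, 0 | 90% | 92% | 96% | 99% |
| 100, 0 | >99% | >99% | >99% | >99% |
| 100, −30 | 87% | 88–89% | 94% | 99% |
| 140, −30 | 59% | 62–63% | 70% | 85% |

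At rho 0 adjustment costs about 1 to 2 points (for example 90% to 89% at SD 143.7). Break-even is near rho 0.2. Type I error of the adjusted test at the margin is 0.023 to 0.026.

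**5. Change score.** With equal SDs its variance is 2(1 − rho) × SD², below the raw variance only if rho exceeds 0.5. At SD 143.7 and Δ = 0 its power is 63%, 78%, 90% and 99% at rho 0, 0.3, 0.5 and 0.7.

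**6. Superiority.** With 200 nmol/L, SD 70 and n=30, power is about 100%, so these tests need no adjustment.

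**The case against.** **The raw test is correct.** In a randomised crossover the unadjusted paired mean is unbiased and holds its type I error. This stands in full: a reader might infer that ignoring baseline biases or invalidates the result, and nothing in the article supports that.

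**The gain may be small.** Rho, SD and Δ are all assumed. SD 140 is close to the largest value compatible with the stated power at zero difference. If the 70 nmol/L given for the superiority tests also described the change-score SD between the two active treatments (which the article does not say), equal SDs would imply raw SDs of 70/√(2(1 − rho)), about 59, 70 and 90 at rho 0.3, 0.5 and 0.7. Raw power would then exceed 99% at Δ = 0 and be at least 92% at Δ = −30. This also stands. A reader might take the last row of the table as showing an underpowered trial; that row needs both a high SD and an assumed shortfall, neither of which is documented.

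**Baseline is used elsewhere.** Both superiority tests and one secondary non-inferiority test use change from baseline, so it would be wrong to say there are two competing primary estimates: absolute is primary, change is secondary. Absolute 30 min cortisol also matches the 430 nmol/L threshold used for NPA. The proposed model keeps that endpoint.

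**The baseline sentence is a joint list.** It covers several analyses, so the mismatch may be only one of wording. Even so, it names the primary non-inferiority analysis explicitly and needs reconciling.

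**Adjustment has costs.** It needs both baselines, and it makes a margin that already allows for baseline variation easier to meet. Missing baselines should be few, since visits lacking key samples are repeated. The margin point is fair and is dealt with in the fix.

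**Conclusion.** The point holds as one of efficiency. The primary non-inferiority test leaves out a covariate that is measured at every relevant visit, that the protocol names as a source of variation, and that one section calls crucial to this very analysis. Adjustment reduces residual variance by about rho²: negligible gain, or a loss of 1 to 2 power points, at rho 0 to 0.2; modest at 0.3; material at 0.5 and above. In power terms the benefit ranges from nothing (SD 100, Δ = 0) to about 5 points (SD 140, Δ = 0, rho 0.5: 91% to 96%), and more if Nasacthin has a true shortfall. All of these rest on assumed SD, Δ and rho, and on equal SDs at baseline and 30 min where the change score is concerned.

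A reader might also infer that the 88 nmol/L margin is too wide by a known amount. The article does not give the size of the baseline allowance, so that cannot be said. It is a change worth making, not a flaw that undermines the trial.

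**What to change.** Before database lock:

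1. Keep absolute 30 min serum cortisol as the primary endpoint. Regress the within-participant Nasacthin-minus-Synacthen difference on the corresponding baseline difference, or fit an equivalent within-participant model, and test the intercept against the margin.
2. Keep the unadjusted paired mean as a sensitivity analysis, which also covers participants with a missing baseline.
3. Use the same adjustment for the 60 min serum cortisol and salivary cortisone non-inferiority tests. Leave the superiority tests as they are.
4. Reconcile Outcomes and assessments with Final analysis on whether baseline enters the primary non-inferiority analysis.
5. Re-justify with the regulator the part of the 88 nmol/L margin added for baseline variation, since adjustment removes some of that variation.

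Cost: one degree of freedom, a change of wording in the protocol and analysis plan, and a discussion with the regulator. No extra samples or participants are needed.

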The Nasacthin test, which uses an intranasal formulation of tetracosactide (the active pharmaceutical ingredient (API) in Synacthen), has been developed to address this unmet need. Within the Nasacthin formulation, tetracosactide is coupled with chitosan, a mucoadhesive agent, in order to aid nasal absorption. This can be administered nasally via a spray, with the resultant glucocorticoid levels measured in saliva samples to quantify the adrenal response.

Salivary glucocorticoid estimation is growing in popularity due to the advantages of non-invasive sampling and close correlation between salivary cortisol and cortisone, and biologically active free serum cortisol. Salivary cortisol is a validated, well-established alternative to invasive glucocorticoid sampling, and is recommended as a first-line diagnostic test for Cushing’s syndrome.^8^ It has also been investigated following Synacthen stimulation in healthy volunteers and patient populations,^9 10^ and specifically following Nasacthin administration in healthy adult males and children.^11^ However, it is salivary cortisone that has emerged as the preferred salivary biomarker as, due to rapid metabolism of salivary cortisol to cortisone, it is the more abundant glucocorticoid and gives a closer reflection of serum cortisol levels, with better sensitivity at low serum cortisol levels.^10 12 13^ A recent prospective diagnostic accuracy study showed that the waking salivary cortisone level was a strong predictor of the serum cortisol response to Synacthen in the SST.^14^

To date, four pharmacokinetic-pharmacodynamic studies (PK-PD)and a reproducibility study have been completed,^11^ in which a total of 70 doses of Nasacthin have been administered to healthy adult males and children. All participants were dexamethasone suppressed to allow quantification of ACTH_(1–24)_ for PK analysis. These studies found Nasacthin to be reliably absorbed and well tolerated, and importantly demonstrated a comparable plasma cortisol response to the intravenous Synacthen test, and that 60 min is the optimal timing of salivary glucocorticoid sampling following Nasacthin.^9^

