**Figure 1 F1:**
[figure not shown]
Flow diagram of study procedures. IV, intravenous.

Participants will be contacted at 5 and 2 days prior to each visit to confirm attendance and perform essential checks around visit-specific exclusions. Participants will be asked to abstain from alcohol consumption and recreational drug use for 24 hours and liquorice ingestion within the last week (preparations containing glycyrrhizic acid only), while any nasal visits will be rescheduled if a participant has experienced coryzal symptoms in the last week, or a heavy nosebleed in the previous 48 hours, due to the unknown effect on nasal absorption.

Study visits will commence between 08:00 and 09:00, in order to obtain samples for baseline glucocorticoid determination while cortisol levels are near their physiological peak. At the first study visit, basic demographic data will be collected, and height and weight will be measured. The height and weight measurement will be repeated at subsequent visits for any children who have more than 3 months between visits.

At the start of each visit, a set of baseline clinical observations (temperature, pulse rate, blood pressure and respiratory rate) will be taken to confirm the participant is well, and all participants of childbearing potential will require a confirmed negative pregnancy test before study activities can commence at each visit, due to the potential for altered cortisol levels, and in accordance with the recommendation that Synacthen should not be administered in pregnancy.^17^

Following intravenous cannulation, participants will rest supine for a minimum of 20 min. Participants will be requested to rinse their mouths thoroughly with water 10 min prior to commencing sample collection, after which a pair of baseline blood and saliva samples will be collected. All blood samples will be taken from the indwelling cannula and all saliva samples (minimum 1 mL per sample) will be collected by passive drool into a Saliva Collection Aid (Salimetrics, Pennsylvania, USA).

Whole blood samples will be collected in serum separating tubes, and will be gently mixed and left to clot for 30–60 min at room temperature, before centrifuging at 1300 *×g* for 10 min. Resulting serum will be aliquoted into cryovials for storage. Saliva samples may be centrifuged at 1000 rpm to reduce bubbles if necessary. All samples will then be transferred to −80°C freezer storage prior to shipment to a central laboratory for analysis.

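### Salivary cortisone at 60 min has no stated comparison with placebo, so its non-inferiority result alone cannot show that saliva responded to either drug

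*Protocol article*

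**What the plan says.** All references are to the protocol article.

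- **Placebo comparisons.** Outcomes and assessments limits them to one variable and time: "The mean change from baseline in serum cortisol concentration at baseline and 30 min after Nasacthin and Synacthen stimulation will also be separately compared" with the matching placebos. The Abstract and Sample size sections agree; the superiority power statement is for serum cortisol.
- **Salivary test.** Under Final analysis, the 60 min secondary objectives "will use the same methodology as the primary non-inferiority objective", but "they will use the 60 min timepoint and, for salivary cortisone, the non-inferiority margin will be set at ±25 nmol/L". The primary non-inferiority comparison is Nasacthin against Synacthen on paired means and "will be assessed using a one-sided test". Outcomes and assessments adds the change from baseline in salivary cortisone, again between the two active drugs.
- **Exploratory summary.** Final analysis describes salivary cortisol and cortisone at 30 and 60 min after the active treatments only.
- **Hierarchy.** Both serum superiority tests must be significant first. The primary non-inferiority and NPA tests follow by truncated Hochberg. If at least one succeeds, the secondary non-inferiority tests share the remaining alpha by Hochberg.
- **Role of the salivary marker.** The Introduction says "it is salivary cortisone that has emerged as the preferred salivary biomarker" and gives 60 min as the best sampling time after Nasacthin.
- **Setting.** Participants are not dexamethasone suppressed (Study population). Visits start in the early morning "while cortisol levels are near their physiological peak" (Study procedures). Paired blood and saliva are taken at every visit, placebo visits included.

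**The concern.** A non-inferiority test shows that one treatment is not much worse than another. It does not show that either had an effect. If neither drug moved salivary cortisone, the true difference would be 0, which is well inside the margin. In unsuppressed participants sampled in the morning, each active visit carries an endogenous cortisone level, so similar salivary values after both drugs could reflect background and not stimulation. The placebo visits are the trial's own means of telling the two apart.

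The plan already applies this logic to serum, where both active drugs must beat placebo before serum non-inferiority is tested. It does not extend the safeguard to the matrix, analyte and time at which the Nasacthin test is meant to be read. What is at stake is how a positive salivary result may be interpreted.

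**Working it through.** **Inputs from the article.** n=30 (Sample size); salivary margin 25 nmol/L, applied as a lower limit of −25 in a one-sided test; alpha 0.025, taken from the primary test: "The significance level (alpha) used for the non-inferiority test has been nominally set at 0.025". The alpha actually available to the secondary tests depends on earlier results, so other values are shown.

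**Input not in the article.** The SD of the paired Nasacthin-minus-Synacthen difference in salivary cortisone. It is assumed and varied from 20 to 80 nmol/L.

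**Step 1: reproduce a stated figure.** The superiority power statement is the only one whose inputs are all given: difference 200 nmol/L, SD up to 70, two-sided 5%. The non-centrality is 200 × √30 / 70 = 15.6, against a critical t (29 df) of 2.045, so power exceeds 99.9%. If 70 is a per-visit SD and visits are uncorrelated, the SD of the difference is 70 × √2 = 99, the non-centrality is 11.1, and power still exceeds 99.9%. The stated >90% holds. No power is stated for the salivary test.

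**Step 2: chance of passing when neither drug moves saliva.** The true difference is 0. Pass probability = P(T > t critical), where T is non-central t with 29 df and non-centrality 25 × √30 / SD.

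| Assumed paired SD (nmol/L) | Non-centrality | alpha 0.05 | alpha 0.025 | alpha 0.0125 |
|---|---|---|---|---|
| 20 | 6.85 | >99.9% | >99.9% | >99.9% |
| 30 | 4.56 | 99.8% | 99.3% | 98.3% |
| 40 | 3.42 | 95.5% | 91.1% | 84.9% |
| 50 | 2.74 | 84.8% | 75.4% | 64.7% |
| 60 | 2.28 | 72.0% | 59.7% | 47.7% |
| 80 | 1.71 | 51.1% | 38.0% | 27.3% |

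At alpha 0.025 the pass probability is at least 90% for any SD up to 40.8 nmol/L.

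**Step 3: a less extreme case.** Suppose Synacthen raises salivary cortisone by 10 nmol/L (an assumed value) and Nasacthin by nothing. The distance to the margin is 25 − 10 = 15. At alpha 0.025 the test passes with probability 97.8% at SD 20 (non-centrality 15 × √30 / 20 = 4.11) and 75.4% at SD 30 (2.74).

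Steps 2 and 3 describe the salivary test once it is reached. They are not probabilities for the whole hierarchy.

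**Step 4: can the existing sample support a placebo comparison?** For a paired test with n=30 at two-sided 5%, power is 97.8% if the active-minus-placebo effect is 0.75 of its paired SD (non-centrality 0.75 × √30 = 4.11) and 99.96% at 1 SD (5.48). In absolute terms, 90% power corresponds to a rise of about 12 nmol/L at SD 20, 18 at SD 30 and 25 at SD 40. The article gives no expected salivary effect, so these figures show only what could be detected.

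**The case against.** The strongest reply is the hierarchy. If neither drug worked, the serum superiority tests would normally fail and the salivary test would not be reached. A reader might infer from Step 2 that the trial could declare salivary non-inferiority with two inert drugs. The article does not support that. The remaining scenario is narrower: serum cortisol rises at 30 min after both drugs, at least one of the non-inferiority and NPA primaries succeeds, and salivary cortisone at 60 min responds little or not at all. The Introduction reports that salivary cortisone follows serum cortisol closely, which makes a complete lack of response unlikely. This stands and limits the concern. It does not remove it, because serum at 30 min is another matrix, analyte and time, and the Nasacthin development studies cited there were in suppressed participants.

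Second, a flat response would be partly visible. The change from baseline in salivary cortisone is compared between the active drugs, and the pharmacodynamic section correlates serum cortisol with salivary cortisone. With baseline near the morning peak, endogenous drift would tend to be downward, so a clear rise after both drugs would be hard to attribute to drift. This also stands in part. Change from baseline, however, has no placebo control for time of day, and the stated purpose of the correlation is exposure estimation.

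Third, the article is condensed, and a descriptive salivary comparison with placebo may exist in the full protocol or SAP. That is fair, and the absence of a descriptive table is not the point. The article does set out its superiority comparisons and testing order, and saliva against placebo is in neither.

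Fourth, salivary non-inferiority is a secondary objective, diagnostic performance in patients is left to STARLIT-3, the design is described as agreed with the regulator, and recruitment opened in January 2024. These points bear on priority, not on the logic.

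It is also tempting to ask for the same condition on 60 min serum cortisol. That goes too far: the same analyte and matrix must already beat placebo at 30 min for both routes before any non-inferiority test.

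**Conclusion.** The concern holds in a limited form. No salivary cortisone comparison with placebo is stated, and the salivary non-inferiority test cannot by itself separate a shared response from a shared lack of one. If it is reached and there is no salivary effect, it passes with probability about 99% at a paired SD of 30 nmol/L, 91% at 40, 75% at 50 and 38% at 80 (n=30, one-sided 0.025). These figures rest on assumed SDs and on the alpha left by the earlier tests. A reader might infer that the test would certainly pass; without an SD in the article that cannot be said. The article's stated figures are not wrong on this point. The gap is in what a positive salivary result can be taken to mean.

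**What to change.** Add two paired comparisons of the 60 min change from baseline in salivary cortisone: Nasacthin against nasal placebo, and Synacthen against intravenous placebo, each at two-sided 5% with confidence intervals. State that salivary non-inferiority will be interpreted as a comparable stimulated response only if both show superiority. Because both are required, in addition to the existing test, no alpha is spent. Leave the 60 min serum cortisol objective as it is.

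The cost is protocol and SAP wording, with any approval that a change to the stated hierarchy needs while the trial is under way. No new samples, visits or participants are required. The downside is that a secondary claim carries one more condition and also depends on placebo-visit data.
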